## Abstract

**Introduction:**

Bipolar disorder has a long depressive episode and high risk of suicide. In clinical practice, patients often show no response to pharmacotherapy, which results in prolongation of the depressive episode. Repetitive transcranial magnetic stimulation (rTMS) is a non-invasive technique expected to serve as a treatment option for bipolar depression. For bipolar depression, a meta-analysis suggested that low-frequency stimulation to the right prefrontal cortex was possibly effective. However, a medium or large sample, randomized, double blind, sham controlled study has not yet been performed.

**Objective:**

To examine the efficacy and safety of 1-Hz rTMS to the right prefrontal cortex in patients with treatment-resistant bipolar depression. rTMS was approved by the Ministry of Health, Labor, and Welfare as a highly advanced medical technology on March 1, 2019.

**Methods:**

In this multicenter, double-blind, randomized, sham stimulation-controlled trial for bipolar depression, patients will be individually allocated to active or sham stimulation plus usual medication and followed up for 6 months. The conditions of stimulation by the Mag Pro R30 transcranial magnetic stimulation device (Magventure) will be a frequency of 1-Hz, intensity of 120% motor threshold, and duration of 1800 seconds to the right prefrontal cortex 5 days a week for 4 weeks during the acute treatment period. The primary endpoint will be a total change in the Montgomery-Åsberg Depression Rating Scale score during the acute treatment period.

**Discussion:**

The outcomes of this study will inform clinical practice for the treatment of bipolar depression.

**Clinical trial registration:**

https://jrct.niph.go.jp/latest-detail/jRCTs032180138, identifier jRCTs032180138.

## Introduction

Bipolar depression is a mood disorder consisting of depressive, manic, and hypomanic episodes. It has a high recurrence rate, rapidly advances to more severe episodes, severe disability, and frequently takes a chronic course (1, 2). Patients with bipolar depression also have a high risk of suicide attempt and a manic switch (3). Patients spend most of the time in a depressive state. According to the treatment guidelines developed by the Japanese Society of Mood Disorders, depressive episodes of bipolar depression (4) are treated with mood stabilizers or atypical antipsychotics, specifically quetiapine (300 mg/day), lithium (0.8 mEq/L of blood concentration), olanzapine (5–20 mg/day), lurasidone (20–60 mg/day), or lamotrigine (200 mg/day). However, in clinical practice, patients often show no response to pharmacotherapy, which results in prolongation of the depressive episode and difficulty in achieving remission. Other recommended treatments by the Japanese Society of Mood Disorders include the combined use of lithium (0.6–0.8 mEq/L of blood concentration) and lamotrigine (200 mg/day), therapeutic dose of lithium or valproic acid and lamotrigine, or electroconvulsive therapy (4). ECT requires pretreatment with intravenous anesthetics and muscle relaxants and may cause temporary memory impairment, including amnesia. Thus, it is necessary to develop therapeutic methods to treat intractable bipolar disorder given the limited number of treatment options. Transcranial magnetic stimulation (TMS) is a non-invasive technique that stimulates the brain through the generation of an eddy current, which appears in association with a variable magnetic field forming around a coil supplied with an electrical current. Delivery of the TMS pulses in short intervals is referred to as repetitive TMS (rTMS). High-frequency stimulation affects cortical excitability in a facilitatory manner (5), whereas low-frequency stimulation suppresses cortical excitability (6). In Japan, rTMS has been approved by the Ministry of Health, Labor, and Welfare as an insurance-covered therapeutic method for the treatment of refractory major depressive disorder. Many clinical studies used rTMS to treat refractory depression, but only a few studied bipolar disorders. To address this issue, Zengin et al. (7) showed that rTMS treatment to the left prefrontal cortex is effective and safe for 29 participants with treatment-resistant bipolar depression by randomized controlled trial. McGirr et al. (8) showed a double-blind, 4-week, randomized clinical trial for 37 participants of intermittent theta burst stimulation (iTBS) to the left dorsolateral prefrontal cortex (DLPFC). The iTBS to the left DLPFC was not efficacious in the treatment of bipolar depression. A systematic meta-analysis of randomized double-blinded comparative studies on depression, bipolar disorder, or both was performed to assess the treatment efficacy for bipolar disorder. A total of 19 clinical studies that met the quality criteria were included, involving 181 patients with bipolar disorder (9). This meta-analysis showed that the response rate for patients receiving active stimulation was 44.3%, whereas it was 25.3% for sham stimulation, suggesting that the treatment was effective in those receiving active stimulation for bipolar depression (9). The therapeutic efficacy was compared based on the number needed to treat (NNT); the NNT in the active stimulation group was 6 (95% confidence interval [CI], 4–15) compared to the control sham stimulation group. The NNT for high-frequency stimulation to the left prefrontal cortex was 7 (95% CI, 4–112), whereas that for low-frequency stimulation to the right prefrontal cortex was 3 (95% CI, 2–6) (9), suggesting that low-frequency stimulation to the right prefrontal cortex was possibly more effective. A single-blind randomized sham-controlled trial for 54 patients with antidepressant-nonresponding bipolar depression was performed (10). They concluded that 1-Hz 110% motor threshold and 300 pulses rTMS to the right prefrontal was not effective for bipolar depression over sham control. This failure was possibly attributed to a stimulus parameter (300 pulses/session for 15 sessions, with a total of 4,500 stimulation). Kito et al. conducted a preliminary study in which low-frequency stimulation was applied to the right prefrontal cortex and reported that the treatment was effective (11), safer, and more tolerable than high-frequency stimulation, a standard method of stimulation, applied to the left prefrontal cortex (11). The addition of 1-Hz 120% motor threshold and duration of 1,800 s (1,800 pulses) to the right prefrontal cortex rTMS to the usual medication will provide superior improvement of depressive symptoms compared to medication as usual for bipolar depression. However, a medium or large sample randomized, double-blind, sham-controlled study in this parameter has not yet been conducted. Therefore, as a therapeutic option for bipolar depression, we designed a medium sample, double blind, randomized, sham-controlled trial of low frequency (1,800 pulses/session for 20 sessions, with a total of 36,000 stimulation) to the right prefrontal cortex. This study aims to examine the efficacy and safety of 1-Hz rTMS to the right prefrontal cortex of patients with treatment-resistant bipolar depression. rTMS for bipolar depression was approved by the Ministry of Health, Labor, and Welfare as a highly advanced medical technology on March 1, 2019.

## Materials and methods

### Trial design

This study will be a multicenter, double-blind, randomized, sham stimulation-controlled trial. Patients will be individually allocated to 1-Hz rTMS plus usual medication (intervention group) or sham stimulation plus usual medication (control group) and followed up for 6 months. A summary of the EASyS-BD diagram is illustrated in **Figure 1**.

**Figure 1 f1:**
[figure not shown]
Flowchart summarizing the trial.

### Study setting

This study will comply with the Clinical Study Act (enacted in 2017, law number 16) and will be conducted with maximum attention paid to the dignity of individual study participants, respect of human rights, and protection of personal information. Participants will be recruited from three psychiatric departments: the National Center of Neurology and Psychiatry, Tokyo, Japan; Jikei University School of Medicine, Tokyo, Japan; and Keio University, Tokyo, Japan.

### Number of participants

Number of participants who obtained consent: active stimulation group, 48; sham stimulation group, 48; total, 96 (1:1 randomization).

Number of participants analyzed: active stimulation group, 38; sham stimulation group, 38; total, 76 (1:1 randomization).

A meta-analysis performed by McGirr et al. included patients with a depressive episode of bipolar disorder, and the effect size in the amount of change in depressive symptoms was 0.48 for low-frequency stimulation to the right prefrontal cortex (9). Since there were no previous studies on concomitant pharmacotherapy in bipolar disorder, the effect size was estimated as 0.65 based on the results of the aforementioned meta-analysis. The sample size was estimated assuming the effect size of 0.65, two-sided alpha equal 0.05, and power of 0.80. Overall, 80% of participants will be considered appropriate to be included in the double-blind study according to the inclusion and exclusion criteria. Therefore, with the sample size multiplied by 1/(1–0.20), the number of participants who will need to provide consent is 48 for each group; thus, we will need to recruit 96 participants.

### Recruitment

Outpatients from three medical institutions will be recruited. Advertising will be conducted through a web homepage and medical magazines to enhance recruitment.

### Eligibility criteria

Participants will be assessed for eligibility using the study-specific inclusion/exclusion criteria during the screening visit.

### Inclusion criteria

Patients will be included if they meet the following criteria:

Patients who meet the diagnostic criteria of bipolar disorder including types I and II with depressive episodes according to the *Diagnostic and Statistical Manual of Mental Disorders 5th Edition* (12) (DSM-5). However, in the case of a rapid cycler or mixed episode, the patient will be excluded from the study.Patients aged 20 years or older and 75 years and younger at the time of consent.Patients with a total 17-item Hamilton’s Rating Scale for Depression (HAMD-17) (13) score ≥18.Patients who have had a depressive episode within the last 3 years.During the current depressive episode, patients who have not responded to any of the following pharmacotherapies for more than 8 weeks without antidepressants (4).

 - Lithium, ≥0.8 mEq/L blood concentration - Quetiapine, 300 mg/day - Olanzapine, 5–20 mg/day - Lurasidone, 20–60 mg/day - Lamotrigine, 200 mg/day

The reason for setting each inclusion criterion is discussed below.

The reason for the use of HAMD-17 as an inclusion criterion is that a previous study conducted by O’reardon et al. (14). and other studies on magnetic stimulation employed HAMD-17 as an inclusion criterion and evaluated the efficacy with MADRS as the primary endpoint. The pilot study of refractory bipolar disorder conducted by Kito et al. also used HAMD-17 as an inclusion criterion and MADRS for the main efficacy evaluation. Thus, the reason for using HAMD-17 as an inclusion criterion is to be consistent with the large exploratory study of rTMS (conducted by O’reardon et al.), thereby enabling comparison. The reason for using MADRS instead of HAMD-17 for efficacy evaluation is that HAMD-17 has more parameters to evaluate sleep and allocates higher scores to the conditions than MADRS does. Therefore, similar to these evaluations, this study has also been designed to use HAMD-17 as an inclusion criterion and MADRS as the primary endpoint. Furthermore, we selected a total score of 18 or more in HAMD-17 because this was used as an inclusion criterion in the study of O’reardon et al. and because this study examines moderate or more severe bipolar disorders.

### Exclusion criteria

Patients will be excluded if they meet the following criteria:

Patients with a history of mental illness such as obsessive–compulsive disorder, post-traumatic stress disorder, or eating disorder.Patients who have received neuromodulation such as ECT, rTMS, vagus nerve stimulation, deep brain stimulation, or transcranial direct current stimulation.Pregnant patients.Patients with a history of convulsive disorders such as epilepsy or patients whose close relatives (first-degree family members) have convulsive disorders.Patients with a history of neurological disorders or organic brain disorders.Drug- or alcohol-dependent patients.Patients with magnetic material such as pacemakers, cochlear implants, or intracranial clips.Patients with physical disorders such as serious metabolic diseases or endocrine disorders.Patients with significant suicidal ideation (HAMD-17 score for suicide, ≥3).Patients who are receiving pharmacotherapy that modifies the threshold of seizure (e.g., neuroleptics and tricyclic antidepressant agents).Patients considered inappropriate by the investigator/physician representing the study.

### Randomization, allocation concealment

Cases will be enrolled and assigned to each stimulation group by the staff in charge of assignment in a centralized and aggregated manner. The subjects will be assigned with stratified block randomization. The stratified factors are sex and age (20–50, 51–75 years). Magventure will prepare the assignment table (corresponding table) on which six-digit patient codes are filled in, and the staff in charge of assignment will assign subjects to the actual or sham stimulation groups based on the assignment table. The staff in charge of assignment and the staff supporting the personal information management will not be allowed to recruit subjects, obtain IC, or perform intervention or neuropsychological testing.

The specific procedure is as below:

The staff in charge of recruiting study subjects and obtaining their informed consent (IC) will perform necessary assessment on the candidate patients according to the inclusion and exclusion criteria, after obtaining their written consent.The case enrollment form on which prescribed information are filled in will be sent to the staff in charge of assignment to apply for enrollment and assignment.After confirming the condition of the study subjects, the staff in charge of assignment will fill in the case enrollment number and six-digit patient code on the enrollment confirmation based on the assignment table prepared in advance and send it back to the study staff in each medical institution.The study staff in each medical institution will receive the enrollment confirmation, which contains the case enrollment number and patient code, from the staff in charge of assignment.

### Blinding and unblinding

Patients, investigators, and the evaluator will be blinded. The emergency key for unblinding will be kept by the staff in charge, and assignment will not be disclosed, except for in emergency cases. Unblinding of the data will be performed only after completion of this study and fixation of the data. The emergency key for unblinding will be kept by the staff in charge of assignment and not be disclosed, except for emergency cases. Unblinding will not be allowed to determine future therapy.

### Intervention

#### Information on the medical devices

Based on a preceding study by McDonald (15), the conditions of stimulation by the Mag Pro R30 TMS device (Magventure) will be a frequency of 1 Hz, intensity of 120% motor threshold, and duration of 1,800 s (1,800 pulses) to the right prefrontal cortex, defined by the Beam F3 Location System (16), 5 days a week for 4 weeks during the acute treatment period, followed by a 3-week gradual reduction period (**Figure 2**). rTMS in a 3-week gradual reduction period will gradually reduce to 3 days a week in the first week, 2 days a week in the second week, and 1 day a week in the third week. Beam et al. have developed to find the F3 position using three skull measurement systems. The measurement of F4 (right DLPFC) is defined by Beam et al. (16) as follows:

Measurement of the distance from tragus to tragus and marking of the midpointMeasurement of the distance from nasion to inion (the midpoint is marked here as well, and the vertex is the point where the two lines containing the midpoints meet)Measurement of head circumference: Once these three measurements are attained, they are entered into the software package which provides two output values (values X and Y).A point along the circumference is marked X cm from the midline.F3 is marked as a point along the line running from the vertex through the point created in the previous step Y cm from the vertex.The “x” at the top of the head is the vertex; the other “x” is the F3 location.The opposite side of F3 from the midline is F4.

**Figure 2 f2:**
[figure not shown]
Schedule of informed consent, baseline, acute treatment period, gradual reduction period, observation period.

The stimulation coil Cool-B65 A/P (Magventure) will be used. This coil was developed for use in clinical studies, and its internal system allows for assignment to the active or sham stimulation group under double-blind conditions. Assignment to the active or sham stimulation will be determined by the six-digit patient code that will be assigned to each patient in advance. In the active and sham stimulation groups, a stimulating electrode will be placed on the participant’s scalp to deliver weak sensory stimulation in synchronization with pulses; thus, the participants will not be able to differentiate between sham or active stimulation. In sham stimulation, although the same sensory stimulation will be administered as in actual stimulation, the intensity will not be enough to reach the brain. This system will ensure a blinded process for participants receiving sham stimulation in the control group. Both participants and staff will be unable to determine whether the stimulation is active or sham.

### Conditions of concomitant drug and combination therapy

Medication such as lithium (>0.8 mEq/L blood concentrations), quetiapine (>300 mg/day), olanzapine (5–20 mg/day), lamotrigine (>200 mg/day), or lurasidone (20–60 mg/day), which will have been administered before the start of the study, and psychiatric therapy may be continued throughout the study under the same conditions. Additionally, eszopiclone at the maximum dose of 3 mg or zolpidem at the maximum dose of 10 mg as hypnotics and lorazepam at the maximum dose of 3 mg as anxiolytics will be administered as needed. ECT will be prohibited during the study period since it has a profound effect on the evaluation of the treatment efficacy.

### Evaluation

The screening visit will commence after each participant has been enrolled. The schedule of examinations is listed in **Figure 3**.

Demographic variables and clinical observation information: Information including sex, age, main diagnosis, and disease duration are obtained from interview or medical records.Psychological test parameters: face-to-face evaluation (interview)Psychological test parameters: questionnairePsychological test parameters: cognitive functioning testAssessment will be performed for items related to suicide in HAMD-17 and Young Mania Rating Scale (YMRS) for each rTMS delivery.

**Figure 3 f3:**
[figure not shown]
Standard protocol items: Schedule of enrollment, interventions, and assessments. rTMS, repetitive Transcranial Magnetic Stimulation; SCID-1, Structured Clinical Interview for DSM-4-TR Axis I Disorder; MADRS, Montgomery-Asberg Depression Rating Scale; HAMD-17, Hamilton's Rating Scale for Depression 17-item; PHQ-9, Patient Health Questionnaire; CGI, Clinical Global Impression; YMRS-J, Japanese version of Young Mania Rating Scale; EQ-5D, EuroQol 5 Dimensions; BACS-J, Brief Assessment of Cognition in Schizophrenia Japanese version; THINC-it, THINC-integrated tool.

### Data quality

The same participant will be assessed by the same site evaluator throughout the study. A trained and qualified site rater will perform the efficacy and safety assessment. The inter-rater reliability (IRR) of the Montgomery–Åsberg Depression Rating Scale (MADRS) (17) will be confirmed with kappa coefficient. To improve IRR, all raters will be with a training trained using DVD and confirmed.

### Evaluation of adverse events

Safety parameters are evaluated for each rTMS stimulation. Information relating to the adverse event, date of onset, date of resolution, severity, treatment, outcome, seriousness, and relationship to rTMS will be described in the medical record and case report form. When the relationship to rTMS cannot be ruled out, follow-up observations will be performed as much as possible until recovery to normal conditions. The terms used to describe adverse events conform to those provided by the Medical Dictionary for Regulatory Activities/Japanese version (MedDRA/J): International Conference on Harmonization (ICH).

The safety evaluation parameters are as follows:

Adverse events, particularly headache, stimulation site pain, stimulation site discomfort, presence or absence of muscle contraction (evaluated each time rTMS is delivered).The presence or absence of suicidal ideation (a parameter related to suicide in HAMD-17) and YMRS score (evaluated each time during the acute treatment and observation periods).

The results of the safety evaluation parameters should be recorded on the case report each time they are evaluated.

The severity of each adverse event is defined as follows:

Mild: the condition in which the participant feels discomfort but does not interfere with daily life.Moderate: the condition that restricts the participant’s daily life and makes the participant feel uncomfortable.Severe: the condition wherein the participant is unable to work or perform daily activities.

### Compensation

If serious health hazards, including death, occur as a result of participation in this study, the participants can receive payment of compensation from the insurance that the researcher has purchased.

### Definition of terms

The terms of the endpoints of this study are defined as follows:

Response: A response will be defined as a decrease of ≥50% in the HAMD-17 score measured at week 0 during the acute treatment period or a total HAMD-17 score of ≤12.Remission: The presence of remission will be defined as a total HAMD-17 score of ≤7.Relapse/recurrence: When a participant experiences conditions that meet the diagnostic criteria for depressive, manic, or hypomanic episodes defined in the DSM-5 after remission, during the acute treatment period, such conditions will be defined as relapse/recurrence. Additionally, relapse will be defined as disease exacerbation within half a year of remission, and recurrence will be defined as disease exacerbation after more than half a year of remission.

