#### Secondary endpoints

The secondary endpoints will be as follows:

Response/remission maintenance rate during the observation period.Relapse/recurrence rate during the observation period.The time to relapse or recurrence during the observation period from the time origin is defined as end of the acute treatment.The change in scores of the MADRS, HAMD-17, Patient Health Questionnaire-9 (PHQ-9) (18), Clinical Global Impression (CGI) (19), Young Mania Rating Scale (YMRS) (20), EuroQol 5 Dimensions (EQ-5D) (21), Brief Assessment of Cognition in Schizophrenia Japanese version (BACS-J) (22), and THINC-integrated tool (THINC-it) (23) during the acute treatment and observation periods.Adverse events, particularly headache, pain at the stimulation site, discomfort at the stimulation site, and muscle contraction on stimulation.Suicidal ideation (suicide subscale score of HAMD-17) and manic switch (YMRS score).

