### Criteria for discontinuation of individual study participant

If the principal investigator, principal investigator, or sub-principal investigator determines that it is not feasible to continue research on an individual research subject for any of the following reasons, the research on that research subject will be terminated. With full consideration given to the ethical aspects of study subjects, information on observations and tests related to the primary and secondary endpoints will be collected after the point of discontinuation to the greatest extent possible.

Withdrawal of consent or request for withdrawal to participate by the study participants.It is revealed after enrollment that the eligibility criteria were not met.Suicidal ideation is exacerbated (HAMD-17 score for suicide, ≥3) and continuation of the study is considered unfavorable.The total YMRS score is ≥8.The occurrence of an adverse event makes it difficult to continue the study.Pregnancy.Significantly poor compliance (rTMS is performed 2 days or less in 2 consecutive weeks).Occurrence of a convulsive seizure.Relapse/recurrence during the observation period.Discontinuation of the entire study, andThe investigator considers it appropriate to discontinue the study for other reasons.

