#### Secondary endpoints

For patients in whom remission is noted at week 4 during the acute treatment period, the days to relapse/recurrence from week 0 during the observation period will be analyzed using the Kaplan–Meier method and log-rank test.

Cox proportional hazards regression analysis will be performed, in which the MADRS total score at week 0, intervention, diagnosis, age, and institution will be explanatory variables.

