#### Other endpoints

The response and remission rates at week 4 in the acute treatment period and at week 28 in the subsequent observation period will be analyzed using logistic regression analysis, in which the MADRS total score at week 0, intervention, diagnosis, age, and institution will be explanatory variables. As a secondary analysis, Fisher test will be used. For MADRS, HAMD-17, PHQ-9, CGI, YMRS, EQ-5D, BACS, and THINC-it, a comparison between the active and sham stimulation groups will be performed using Wilcoxon rank-sum test at week 4 during the acute treatment period and at week 28 in the subsequent observation period, respectively.

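### Response and remission are defined on HAMD-17 alone, so a patient who is manic or hypomanic at the assessed visit with a low HAMD-17 is scored a success, and no rule reconciles this with counting such an episode as relapse

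*Protocol article*

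**What the plan says.** All references are to the protocol article.

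- **Definition of terms, response:** "A response will be defined as a decrease of ≥50% in the HAMD-17 score measured at week 0", or a HAMD-17 total of 12 or less.
- **Definition of terms, remission:** "The presence of remission will be defined as a total HAMD-17 score of ≤7". Neither definition mentions YMRS or polarity.
- **Definition of terms, relapse/recurrence:** "conditions that meet the diagnostic criteria for depressive, manic, or hypomanic episodes defined in the DSM-5 after remission". A manic or hypomanic episode counts here on the same footing as a depressive one.
- **Outcomes, Secondary endpoints:** maintenance of response or remission, relapse or recurrence, and manic switch (by YMRS) are separate endpoints. Nothing links them.
- **Analytical method, Secondary endpoints:** the time-to-relapse analysis is restricted by the remission rule: "For patients in whom remission is noted at week 4 during the acute treatment period".
- **Analytical method, Other endpoints:** logistic regression is applied to "The response and remission rates at week 4 in the acute treatment period and at week 28 in the subsequent observation period".
- **Criteria for discontinuation of individual study participant:** one listed reason is "The total YMRS score is ≥8"; relapse or recurrence in the observation period is another. Neither assigns a response or remission outcome.
- **Definition of case classification:** in the full analysis set, a discontinued patient contributes the values measured up to discontinuation.

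**The concern.** In bipolar depression a low depression score can mean recovery or a change of pole. A definition resting on HAMD-17 alone cannot tell them apart. The protocol treats the second as an unwanted outcome elsewhere: as relapse once remission has occurred, and as a secondary endpoint in its own right. If active stimulation produced more switches than sham, those with a low HAMD-17 at the assessed visit would raise the active arm's response and remission rates, so part of a harm would be reported as efficacy. The time-to-relapse analysis would also start some patients as in remission while they were already in the state it counts as the event.

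**Working it through.** **1. The rules applied to one invented record.** Week 0: HAMD-17 22. Week 4: HAMD-17 5, with a hypomanic episode meeting DSM-5 criteria, first recognised at that visit.

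| Rule | Result |
|---|---|
| Response (fall of at least 50%, or 12 or less) | (22 − 5)/22 = 77%; responder |
| Remission (7 or less) | 5; remitter |
| Week-4 logistic models | success in both |
| Time-to-relapse set | enters, as a week-4 remitter |
| Relapse definition | the polarity it counts, but already present at entry |
| Full analysis set | week-4 value was measured, so it is used |

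The text does not say whether the episode is then an event at the start of observation, an event at the next visit, or no event because it did not begin after remission.

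The second overlap needs no switch at week 4. A genuine week-4 remitter becomes hypomanic during observation with HAMD-17 still at 7 or less. The score rule still says remission; the relapse rule says relapsed. Both feed listed secondary endpoints.

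**2. The denominator.** Number of participants gives effect size 0.65, two-sided alpha 0.05 and power 0.80.

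- n per arm = 2(1.960 + 0.842)²/0.65² = 37.2, rounded up to 38, as stated.
- 38/(1 − 0.20) = 47.5, rounded up to 48, as stated.
- One patient is therefore 1/38 = 2.6 percentage points of an arm's rate.

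**3. Scale against the cited response rates.** The Introduction cites 44.3% active and 25.3% sham, or about 17/38 and 10/38, a difference of 7/38 = 18.4 points. If k of the 17 active responders were switched at the visit (k is assumed) and no longer counted, the difference is (7 − k)/38:

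| k | 0 | 1 | 2 | 3 | 4 |
|---|---|---|---|---|---|
| Difference, points | 18.4 | 15.8 | 13.2 | 10.5 | 7.9 |

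**4. Upper illustration for remission.** Every rate here is an assumption. Let r be remission among non-switchers, s the switch rate, and q the share of switchers with HAMD-17 of 7 or less.

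- Literal rate = r(1 − s) + sq; rate with switchers not counted = r(1 − s).
- The two arm differences differ by q(s_active − s_sham), whatever r is.

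With r = 15% in both arms and q = 80%:

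| Switch rate, active v sham | Literal difference | Switchers not counted | Gap |
|---|---|---|---|
| 5% v 0% | +3.25 | −0.75 | 4.0 |
| 10% v 3% | 21.5 − 16.95 = +4.55 | 13.5 − 14.55 = −1.05 | 5.6 |
| 15% v 5% | +6.5 | −1.5 | 8.0 |

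With q = 50% the literal differences are +1.75, +2.45 and +3.5.

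These are upper figures because the formula gives every switcher a scored week-4 value. If only a fraction f has one, and the rest count as non-remitters, the gap becomes f × q × (s_active − s_sham). For 10% v 3% with f = 1/5 (assumed), it is 0.2 × 5.6 = 1.1 points. With equal switch rates the gap is zero, though both arms' rates are too high.

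**The case against.** **The safeguards are real.** YMRS is rated at each stimulation session (Evaluation), on 5 days a week for 4 weeks, and a total of 8 or more is a listed reason to stop. Many switches should surface before week 4. A patient stopped at week 2 may have no usable week-4 HAMD-17 and would be missing, not a success. Relapse in observation is also a reason to stop, which thins the week-28 cases. This stands, and it limits the size. It does not settle how to classify a switch first seen at the assessed visit, or a patient who was not stopped.

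**The contradiction can be overstated.** A reader might infer that the section calls any switch a relapse. It does so only after remission; a direct switch out of depression qualifies only if the HAMD-17 rule has first made the patient a remitter. A reader might also equate a YMRS total of 8 or more with a DSM-5 episode. The documents use the first as a discontinuation criterion and the second to define relapse, and do not equate them.

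**The harm is not hidden.** Manic switch is a separate endpoint, adverse events are compared by arm, and the primary endpoint does not use these definitions. That is correct, but separate reporting does not remove the success credit from the response and remission rates.

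**A depression scale suits a depression outcome.** This is reasonable for change scores. It is weaker for remission here, because remission selects the set in which a manic or hypomanic episode is an event.

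**The full protocol may cover it.** This cannot be excluded. The article does, however, state its endpoint definitions explicitly, and as stated they give the result above.

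**Conclusion.** The point holds as a gap in stated definitions affecting secondary and other endpoints: response and remission rates at weeks 4 and 28, the maintenance rate set against the relapse rate, and entry to the time-to-relapse set. The MADRS comparison at week 4 is untouched.

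The firm figure is 2.6 points of an arm's rate per affected patient, taking 38 per arm. The total cannot be stated, because the documents give neither a switch rate nor the share of switchers with a low HAMD-17. The scenario gaps of 4.0 to 8.0 points (q = 80%) are upper illustrations. The middle one, 5.6, falls to about 1.1 if one switcher in five has a scored week-4 value. Even the +4.55-point literal difference is about half the standard error of a difference between arms, √(0.215 × 0.785/38 + 0.1695 × 0.8305/38) = 9.0 points.

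It would go too far to conclude that every switch is credited as efficacy or that the arm contrast is necessarily biased. The first ignores stopping and missing values; the second requires switch rates that differ between arms.

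**What to change.** 1. In Definition of terms, add to both response and remission that the patient is not in a DSM-5 manic or hypomanic episode at the same visit.
2. Apply that condition to the week-4 and week-28 rates under Other endpoints, and to entry to the time-to-relapse set under Analytical method, Secondary endpoints.
3. As a sensitivity definition, replace the episode condition by a YMRS total below 8 at that visit. This borrows the protocol's own figure to classify outcomes only; no treatment or stopping rule changes.
4. Do not make anyone who met a manic criterion at any time up to the visit a failure in the main definition. That is a different composite: a patient with a brief rise early on who is well at week 4 or week 28 would fail. It can be a further sensitivity analysis.

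Cost: an amendment of a sentence or two. YMRS is already recorded, and the DSM-5 judgement is already needed to identify relapse; if the week-4 form does not capture it, one item must be added, and for patients already past week 4 it must come from the record. Response and remission rates may be slightly lower. The article reports the trial as still recruiting, with unblinding only after the data are fixed, so the change can be made without knowledge of the results by arm.
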